## **6.Outcome Measure**

### **6.1 Primary Outcome**

The primary outcome for the study is the difference of SBP between baseline and at 24 months of intervention.

### **6.2 Secondary Outcome**

1. The incidence of hyperkalemia : as the main safety evaluation index. According to the 2012 Kidney Disease Improving Global Outcomes (Kidney Disease Improving Global Outcomes), serum potassium > 5.5 mmol/L is diagnosed as hyperkalemia; continuous measurement of serum potassium > 5.5 mmol/L is persistent hyperkalemia. Otherwise, it is a single attack.
2. The change in 24-hour urinary sodium、potassium and microalbumin
3. The change in diastolic blood pressure
4. European Five-Dimensional Health Scale (EQ-5D) score
5. Endpoint events (death, cardiovascular events (coronary heart disease, congestive heart failure, arrhythmia, stroke))
6. Fundus Atherosclerosis

## 6.3 Compliance evaluation

- Proportion of nursing homes that 100% use salt substitute in the SS group
- The proportion of nursing homes that reduce their salt usage by more than 20% in the SSSC group
- Satisfaction level of the elderly in intervention groups

## 7. Safety Considerations

### 7.1 Risk-Based Safety Monitoring and Management Plan

- **All participants will be screened for hyperkalemia and its related risk factors during the baseline investigation, Month 12 follow-up, and Month 24 follow-up.**

All participants enrolled in the trial will be tested for blood potassium and blood creatinine levels during the baseline investigation. Meanwhile, the information about the antihypertensive drugs (ACEI, ARB, potassium-sparing diuretics, etc.) taken by the participants will also be collected.

All participants enrolled in this trial will be tested once again for blood potassium and blood creatinine levels during the Month 12 and Month 24 follow-up.

- **Based on the results of the screening, any elderly who fit the clinical diagnostic criteria for hyperkalemia will be transferred to a local secondary hospital or above for further blood potassium and ECG testing. They will then be treated for hyperkalemia confirmed by the doctor. The elderly who are not diagnosed with hyperkalemia but fit any of the following conditions will be designated as the high risk group for monitoring.**

1. Participants with blood potassium  $>5.5\text{mmol/L}$ ;
2. Participants with  $15 \leq \text{eGFR} < 30\text{mL/min/1.73m}^2$  (Patients with Stage 4 chronic renal insufficiency).

The high risk group for monitoring will receive a blood potassium test every 3 months. Participants who are clinically diagnosed with hyperkalemia will be transferred to a local secondary hospital or above for hyperkalemia treatment. Participants who are not diagnosed with hyperkalemia will continue to be monitored for blood potassium 3 months later. The monitoring can be stopped temporarily should the blood potassium level of the participants  $\leq 5.5\text{mmol/L}$  in two consecutive tests. Otherwise, they will continue to be tested for blood potassium once every 3 months.

- **Blood potassium monitoring plan for the SS intervention group:**

All participants in the SS intervention group, aside from those who are confirmed to have

hyperkalemia or are placed in the high risk group for monitoring during the baseline examination, will go through an extra safety screening during the third and sixth month after the start of the intervention. Screening method: questionnaire and blood potassium test. A questionnaire will first be given to the participants during the screening. The contents of the questionnaire include whether or not participants had symptoms and physical signs of hyperkalemia and kidney disease, as well as what medication they are currently taking. If the questionnaire reveals that the participants have obvious symptoms, physical signs, and a clear inducement of hyperkalemia (i.e. at least one "Yes" to the questions in the second section of the questionnaire), a blood potassium test will have to be conducted for them. For participants whose questionnaires do not reveal the risk of hyperkalemia, they can be tested for blood potassium if they are willing to draw blood. All participants of the SS intervention group have to go through at least one blood potassium test during the two monitorings. (See Annex 16.6 for details about the questionnaire) Based on the monitoring results (clinical diagnosis of hyperkalemia or high risk group for monitoring), participants will undergo the relevant risk monitoring and treatment as mentioned above.

➤ **Clinical Diagnosis of Hyperkalemia and Handling Scheme (According to the 2012 clinical guidelines of the Kidney Disease Improving Global Outcomes)**

- Participant with a serum potassium of  $>5.5\text{mmol/L}$ :

Immediately notify the nursing home where the participant resides in. The nursing home should take the participant to the hospital for another blood potassium test and ECG examination.

- Should the doctor diagnose the participant sent to the hospital with hyperkalemia based on the blood potassium test and other symptoms, the participant will be recommended to immediately undergo treatment such as taking hydrochlorothiazide, sodium polystyrene sulfonate, or if necessary, undergo emergency intravenous infusion to lower potassium levels. If the participant is currently taking antihypertensive drugs like ACEI/ARB, he/she will be required to stop taking those medicines and switch to antihypertensive drugs such as calcium channel blockers,  $\alpha$ -receptor blockers, and  $\beta$ -receptor blockers or  $\alpha\beta$ -receptor blockers. The participant should also be advised to pay attention to their diet to avoid fresh jujube, peach, banana, tomato, soy, tofu, corn, seafood, bacon and other potassium-rich fruits, vegetables, fish, shrimps, crabs, meats, and nuts. The hyperkalemic patient can return to the nursing home after recovery. A review will be done two weeks later. If the participant's blood potassium level is once again  $>5.5\text{mmol/L}$  and the participant is in the SS intervention group, then he/she will go through treatment to reduce potassium levels and be terminated from the research. Otherwise, the participant will continue to be referred for potassium-lowering treatment and continue to be monitored.

➤ **Early termination of research**

The Participants will be stopped from SS intervention if they presented with three consecutive serum potassium measurements  $>5.5\text{mmol/L}$ . The participants can discuss with the nursing home to be transferred to a nursing home that is not participating in the research. Alternatively, the cooks of the nursing home may prepare food using regular salt just for the participants.

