## **7.3 Other Possible Trial-Related Adverse Reactions**

Gastrointestinal adverse reactions: Participants complain about symptoms such as nausea, vomiting, and diarrhoea. Should these reactions occur, the nursing home should be notified to send the participants to the hospital for treatment. Get a doctor to diagnose if the symptoms are a result from the intervention strategies. If these adverse reactions are due to the intervention strategies of this research, then the participants must be stopped for the research. The participants can discuss with the nursing home to be transferred to a nursing home that is not participating in the research. Alternatively, the cooks of the nursing home may prepare food using regular salt just for the participants.

Changes in blood pressure: The blood pressure of participants who regularly take antihypertensive drugs must be routinely monitored during the research period. If there is a significant decrease in their blood pressure, notify the nursing home and send them to the hospital. Get a doctor to gradually adjust the prescription of the drugs to prevent any fainting incidents that might result from an overly low blood pressure. After the research has ended, conduct a follow-up on the participants who regularly take antihypertensive drugs and monitor the changes in their blood pressure after the salt reduction strategies have ended. The prescription of their drugs should be adjusted to prevent any sudden increase in their blood pressure.

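### Protocol 7.1 terminates SS residents whose potassium is high again at the two-week review and does not say follow-up continues, so early cases can leave the randomised hyperkalaemia comparison

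*Supplement*

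**What the plan says.** Protocol V1.4 section 7.1 sends a resident with potassium above 5.5 mmol/L to hospital for a repeat test and ECG. If a doctor diagnoses hyperkalaemia, the resident is treated, returns to the home after recovery, and is reviewed two weeks later. If the value is again above 5.5 and "the participant is in the SS intervention group, then he/she will go through treatment to reduce potassium levels and be terminated from the research", participation ends. For everyone else: "Otherwise, the participant will continue to be referred for potassium-lowering treatment and continue to be monitored".

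The next paragraph, headed Early termination of research, has a different trigger and a different consequence: "The Participants will be stopped from SS intervention if they presented with three consecutive serum potassium measurements" above the same threshold. The resident may then move to a non-participating home, or "the cooks of the nursing home may prepare food using regular salt just for the participants".

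On testing, section 7.1 says that all enrolled participants "will be tested once again for blood potassium and blood creatinine levels during the Month 12 and Month 24 follow-up". SS residents, apart from those already confirmed or classed as high risk at baseline, also "will go through an extra safety screening during the third and sixth month after the start of the intervention". Section 6.2 names hyperkalaemia incidence "as the main safety evaluation index".

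The SAP defines a new case by potassium above 5.5 mmol/L at month 12 or month 24 (2.3) and imputes no safety outcome (3.4). It fits a mixed logistic model between groups to that outcome (5.3.2.1) and analyses the month-3 and month-6 data within SS only (5.3.3).

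**The concern.** As written, leaving the trial depends on both the arm and the safety outcome. An SS resident with recurrent hyperkalaemia leaves, and a non-SS resident with the same result stays. If the SS resident leaves before month 12, the only two visits at which the SAP can count a case never take place. The loss falls on the protocol's main safety index, and in the arm where potassium-enriched salt is the hazard under study.

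SBP and clinical events are touched as well. A terminated resident gives no later SBP, and would be censored for events at the last encounter under SAP 3.4.

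**Working it through.** **Does any text keep the resident in follow-up?**

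| Place | What it provides | Does it settle the matter? |
|---|---|---|
| Protocol 7.1, month-12/24 tests | Potassium for all enrolled participants | Does not say whether a terminated resident is included |
| Protocol 7.1, Early termination paragraph | Stop SS; transfer or regular-salt meals | Suggests stopping treatment only; silent on visits |
| Protocol 5.5, early withdrawal | Adverse events are a ground for withdrawal; one last visit, best effort | No later visits; its laboratory list does not name serum potassium |
| Protocol 7.4 | Adverse event followed until resolved or stable | Clinical follow-up, not the scheduled tests |

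No passage states that scheduled visits continue.

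**How the case leaves the model.**
1. The SS-only screening at months 3 and 6 can find a high value well before month 12.
2. Hospital diagnosis, treatment and the two-week review can also be complete before month 12.
3. If the resident is then terminated, there is no month-12 or month-24 value.
4. With no imputation (SAP 3.4), the outcome in SAP 2.3 is undefined and the resident does not enter the model in 5.3.2.1.

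A resident first found high at month 12 is already a case, so the problem is confined to earlier exits. Protocol section 9 compares the accumulated number of hyperkalaemia cases with no visit window; the month-12/24 limit comes from the SAP.

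**Size.** The plan gives no figure to reproduce.
- SS homes: 48/2 = 24.
- Planned SS residents: 24 × 20 = 480. After the assumed 20% loss (16 per home, protocol section 10): 24 × 16 = 384.
- Let *a* be the month-12/24 SS cases under full follow-up, and *k* those among them lost through termination. *k* is an assumption.

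Observed SS incidence moves from a/n to (a − k)/(n − k). The fall is k(n − a)/(n(n − k)), which is at most k/n because a ≥ k.

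| k (assumed) | Ceiling, n = 480 | Ceiling, n = 384 |
|---|---|---|
| 1 | 0.21 points | 0.26 points |
| 2 | 0.42 points | 0.52 points |
| 5 | 1.04 points | 1.30 points |

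**On the ratio scale, with assumed rates only.** Take a non-SS risk of 2% and a true risk ratio of 2. Expected SS cases are 480 × 0.04 = 19.2. If a quarter (4.8) are lost, the observed SS risk is 14.4/475.2 = 3.03%, and the observed ratio is about 1.5. If a tenth are lost, it is about 1.8.

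**The case against.** The strongest reply is that the two paragraphs in 7.1 describe one rule. Screening value, hospital retest and two-week review, all above 5.5, make three consecutive measurements. The second paragraph then spells out the action as stopping SS, with regular-salt meals in the same home. Section 7.3 is just as loose ("then the participants must be stopped for the research") and offers the same two options. This reading is plausible. It is not stated, however, and it fits less well if recovery was confirmed by a normal value before the review, since the high values would then not be consecutive. Sites in four regions have to apply the text as it stands.

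A reader might infer that the case disappears from the trial record. It does not. Section 7.2 counts abnormal laboratory data as adverse events, 5.5 asks for safety incidents at the last visit, 7.4 requires recording on the CRF, the safety board reviews safety data twice a year, and SAP 5.3.3 lists cases found by screening. What is lost is its place in the randomised comparison.

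A reader might also infer that a resident moved to regular salt would be counted as non-SS, because the safety set goes by the intervention actually received (SAP 3.3). The documents do not raise this. Such a resident did receive SS, and the model sits under a heading for randomised comparisons. The SAP is silent on a resident who had both salts, which justifies one clarifying sentence and no estimate of bias.

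Nor do the documents support a claim that a real harm would be hidden. Bringing a true ratio of 2 down to about 1.0 requires half of SS cases to be terminated before month 12, and nothing suggests that share.

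One further objection stands in full. A resident who has been treated, taken off an ACEI or ARB and taken off SS may be normal by month 12. Retention alone would then add a non-case to SS and would not count the early event.

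**Conclusion.** The concern holds in limited form. The literal text gives an arm-specific, outcome-dependent exit, and no passage keeps the resident in scheduled follow-up. If sites follow it, the loss from the main safety comparison is informative, and later SBP and event data are lost too.

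The number affected is unknown and probably small, since exit before month 12 requires a high value, a doctor's diagnosis, treatment, and another high value at the two-week review. The k/n ceilings assume that every lost resident would have been a case at month 12 or 24, which is doubtful after treatment. The direction probably favours SS but is not certain, for the same reason. Confidence is medium, because the sponsor may have meant no more than stopping SS. It is worth fixing because the correction is specific and nearly free.

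**What to change.** **Protocol 7.1.** Replace termination from the research with stopping the SS intervention, under one trigger chosen by the clinical team. State that scheduled visits (SBP, month-12 and month-24 potassium, events) continue to month 24 where the resident can be reached.

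**SAP.**
- State that these residents stay in their randomised SS group for the safety comparison.
- Keep the month-12/24 definition as the main result, because those visits are common to all arms.
- Tabulate hyperkalaemia-related discontinuations by arm.
- Add a supportive analysis that counts these residents as cases. Label it an upper bound for SS, because the month-3 and month-6 screening is done in SS only.

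The table and the supportive analysis are needed as well as the retention rule, because retention does not by itself count an early event that has resolved by month 12.

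**Cost.** A wording change, one SAP sentence, one table and one small extra analysis. No new tests are needed, since month-12 and month-24 potassium is already planned for all participants. Residents who transfer to a non-participating home may not be reachable.

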## **7.2 Adverse Events**

Adverse events are any adverse medical incidents that happen to the participant after participating in the research. It does not have to have a causal relationship with the intervention strategies.

Adverse events can be any of the following adverse and unexpected physical signs (including abnormal laboratory data), symptoms, or diseases. It does not have to be related to the intervention strategies.

## **7.3 Other Possible Trial-Related Adverse Reactions**

Gastrointestinal adverse reactions: Participants complain about symptoms such as nausea, vomiting, and diarrhoea. Should these reactions occur, the nursing home should be notified to send the participants to the hospital for treatment. Get a doctor to diagnose if the symptoms are a result from the intervention strategies. If these adverse reactions are due to the intervention strategies of this research, then the participants must be stopped for the research. The participants can discuss with the nursing home to be transferred to a nursing home that is not participating in the research. Alternatively, the cooks of the nursing home may prepare food using regular salt just for the participants.

Changes in blood pressure: The blood pressure of participants who regularly take antihypertensive drugs must be routinely monitored during the research period. If there is a significant decrease in their blood pressure, notify the nursing home and send them to the hospital. Get a doctor to gradually adjust the prescription of the drugs to prevent any fainting incidents that might result from an overly low blood pressure. After the research has ended, conduct a follow-up on the participants who regularly take antihypertensive drugs and monitor the changes in their blood pressure after the salt reduction strategies have ended. The prescription of their drugs should be adjusted to prevent any sudden increase in their blood pressure.

## **7.4 Serious Adverse Events**

A serious adverse event (SAE) is defined as having any of the following outcomes resulting from the intervention:

- Threat to life
- Requiring hospitalization
- Permanent or significant disability and dysfunction

Should an SAE occur during the course of the research, researchers must adopt the suitable treatment measure on the participant immediately and end the trial.

Should an SAE occur, researchers have to find out the details and record the following content, whether or not it has to do with the intervention strategies: Time of occurrence, end time, measures adopted, relationship with the investigational drugs, etc. For expected SAEs that are unrelated to the research, researchers have to conduct the appropriate recordkeeping and report it to the Ethics Committee after the research is over. For unexpected SAEs or SAEs that are related to the research, a report has to be made in accordance with the provisions of the Ethics Committee.

Should any adverse events occur, researchers have to record the following on the CRF: Time of occurrence, level of severity, end time, measures adopted, and outcome.

The severity of adverse events can be classified into the following 3 levels:

- Mild: Light symptoms and physical signs. Usually a one-off event that does not require treatment and will not affect daily activities. Symptoms would automatically be relieved with rest;
- Moderate: Symptoms and physical signs persist for a longer time. Slightly affects daily activities. Will recover with simple treatment;
- Severe: Symptoms and physical signs persist for an even longer period. Severely affects normal work and activities. Will not easily recover with simple treatment.

Researchers must immediately tend to adverse events that occur during the process of the research appropriately and in accordance with medical guidelines. Researchers can increase the number of follow-ups and laboratory tests on the participants if necessary. Follow-ups should be conducted until the adverse event is resolved or until the participant is in stable condition or fully recovers.

## **7.5 Data Safety Monitoring Board**

Data Safety Monitoring Board has been established. This committee will analyze the safety data of the research project 2 times a year. Should the risk of adverse events be clearly larger than the potential benefits of the research project, the Safety Evaluation Committee will recommend that the research be terminated early. Otherwise, the research will continue until the intervention plan is over.

## **8. Data Management**

### **8.1 Data Management Center**

The Data Management Division of Peking University Clinical Research Institute (PUCRI-DM) will be responsible for all data management work of this trial.

### **8.2 Case Report Form Design and Electronic Database Construction**

Investigator will be responsible for drafting a case report form (CRF) for the trial by following the template of the PUCRI-CRF. The draft CRF will be submitted to the PUCRI-DM for their opinions on data management and revision before the final CRF is formed.

The final CRF used by the PUCRI-DM will serve as the foundation for the construction of an electronic database using Epidata software.

### **8.3 Data Management Plan and Data Validation Plan**

The PUCRI-DM is responsible for drafting the "Data Management Plan" and "Data Validation Plan" for the research.

Researchers from all sub-sites are responsible for collecting the primary data for the baseline survey and all follow-ups. They should record the data timely, completely, correctly, and clearly on the paper CRF during the collection process. The PUCRI-DM is responsible for constructing an electronic database based on the paper CRF before the start of the research and supplying it to the various sub-sites. The electronic database will not include the names of the participants which will be replaced with serial numbers coding. The respective sub-sites are responsible for the entry of data from the paper CRF to the electronic database, and double entries will be performed by different person respectively. The electronic database will be submitted to the PUCRI-DM after the data entry process. The PUCRI-DM will compare and verify the data. The PUCRI-DM will consolidate all of the queries they found from the data validation, as well as the queries or accidents during the data entry process into a query form. Researchers from the various sub-sites should address these queries until there are no more queries in the data. The data will then be locked in the electronic database for future data analysis and usage.

The paper CRF will be kept and stored by the respective sub-sites. The paper CRF should be filed according to the serial number of the facilities for elderly and stored in its own locked cabinet. A search catalog should also be filled up for easy reference. The manager of the site must be notified whenever the researchers of the sites have to use the CRF for investigation, record, and

data validation purposes. Researchers also have to register at the CRF management logbook. Aside from the personnel responsible for the custody of the paper CRF, no other personnel is allowed to retrieve, read, and modify the data. The PUCRI-DM is responsible for the storage of the electronic data files. This includes the database, verification procedures, analysis procedures, analysis results, codebook, explanatory documents, etc. These files should be classified and stored with multiple backups on different disks or recording media, and be stored appropriately to prevent any damage. Aside from the researchers on this project, no other personnel is allowed to read, use, and modify the electronic data. In addition, the PUCRI-DM shall ensure the safety of the research data.

This plan will be finalized and signed after the PUCRI-DM, researchers, and auditors finalize the research protocol, and before the start of the project. The PUCRI-DM will hold a standardized training on how to fill up and store the paper CRF, enter data into the electronic database, etc. for the researchers of the sub-sites before the start of the baseline survey. They will ensure that the researchers of each sub-site follow the data management requirements specified in this plan.

The "Data Validation Plan" is a document that describes the details of data validation for this project. It will be drafted by the PUCRI-DM after the research protocol and the research CRF are finalized, and then reviewed by the researchers. The "Data Validation Plan" is a document that outlines the points for the data validation and data validating methods based on the requirements of the research protocol and the specific contents of the CRF.

